### Follow-up and assessment of results

All patients will be contacted by telephone 1 and 3 months after the intervention to determine whether they have stopped smoking and, if they have not, how many cigarettes they are smoking per day at the time. One year after the intervention a further phone call will be made by health professionals blinded to the group allocation to assess the patient’s smoking status. For patients that claim to have stopped smoking, the nurse will make an appointment to confirm this using a CO-oximeter that measures the carbon monoxide concentration in exhaled air.

### Study variables

The primary outcome variable will be smoking cessation 1 year after the intervention, as reported by the patient and confirmed by measuring exhaled CO, while the secondary outcome variable will be the number of cigarettes/day for those who continue smoking. Other variables to be assessed include age, sex, body weight and height, BMI, pack-year history, Prochaska’s stage of change, Richmond test score, number of previous attempts to quit smoking, number of periods of abstinence of more than 1 month, use of medication for smoking cessation, respiratory symptoms (coughing, expectoration, degree of dyspnoea), comorbidities (high blood pressure, ischaemic heart disease, cerebrovascular accident, peripheral arterial disease, diabetes), and other habits (alcohol abuse, sedentary lifestyle), as well as spirometry parameters (pre- and post-bronchodilator FVC, FEV1, and FEV1/FVC ratio, predicted FEV1/FVC%). The final outcome measures are to be: CO-oximetry results (in patients who report having stopped smoking), attempts to quit smoking in the previous year, spirometry tests in previous years (excluding that of the study), consultations related to smoking in the previous year (excluding any related to the study), use of medication for smoking cessation in the previous year, use of other methods for smoking cessation in the previous year, and quit rates at 1 and 3 months among those who continue smoking.

Table 1 lists the definitions of the study variables.

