### Objectives

The primary objective of this study is to assess the effectiveness of spirometry testing together with providing patients with information about their results for smoking cessation after 1 year in people older than 40 years of age with a more than 10 pack-year history who have not been diagnosed with COPD (at the outset of the study). The secondary objectives include comparing the quit rates in patients with a new diagnosis of COPD and those with normal lung function, and comparing the change in daily smoking rate between the intervention and control groups.

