## Methods/Design

This is a multicentre, open-label, randomized clinical trial. Study subjects are active smokers older than 40 years of age with a more than 10 pack-year history who have not been diagnosed with COPD, from 39 general practitioner (GP) lists within the province of Gipuzkoa. The following patients will be excluded: any who are older than 80 years of age or institutionalized, as well as any who have a life expectancy of less than 1 year, have undergone spirometry testing within the previous 2 years, have been previously diagnosed with respiratory diseases (asthma, interstitial lung diseases, or COPD) that cause pattern changes in spirometry tests, or have contraindications for spirometry testing (Table 1). This clinical trial has been registered in ClinicalTrials.gov (NCT01821885).

**Table 1 T1:** Definition of the study variables

**Active smoker**	**Diagnosis of chronic obstructive pulmonary disease (COPD)**
Any patient who smokes one or more cigarettes per day will be considered an active smoker.	The criteria for the diagnosis of COPD is a post-bronchodilator FEV1/FVC ratio of < 70% (absolute value).
**Spirometry technique**	**Spirometric patterns**
**Baseline spirometry**: the nurse responsible for the spirometry testing will be experienced in the technique and familiar with the ATS/ERS criteria for acceptability (correct start with back extrapolated volume of <150 ml or 5%, curve with no marks or notches and correct end, with no leaks and lasting at least 6 seconds or with a plateau > 1 second in the volume-time curve).	Spirometry results will be considered within the normal range if FEV1/FVC > 70% (absolute value) and FVC and FEV1 > 80% of the predicted values.
	The pattern is classified as obstructive if FEV1/FVC < 70% (absolute value).
To meet the criteria for repeatability, there must be three acceptable manoeuvres and the FVC and FEV1 values in the two best two must differ by no more than 100 ml.	The pattern is classified as restrictive if FEV1/FVC > 70% (absolute value) and FVC < 80% of the predicted value.
	The pattern is classified as mixed if FEV1/FVC < 70% (absolute value) and FVC < 80% of the predicted value.

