### Statistical analysis

Data will be analyzed on an intention-to-treat basis using SPSS 19.0 software. Given that the primary outcome measure is categorical in nature (whether patients do or do not quit smoking), the final comparison will be performed using chi-squared tests and effect size estimates will be expressed as relative risk (RR), absolute risk reduction (ARR), and number needed to treat (NNT) with the corresponding 95% confidence interval (95% CI). Continuous variables will be assessed with the Student’s t-test, if the data meet the assumption of normality, and otherwise with the corresponding non-parametric test.

If this initial analysis demonstrates the need for multivariate analysis, binary logistic regression analysis will be used. This type of model will allow us to compare the primary outcome measure between groups adjusting for any observed differences, and thus minimizing the potential for confounding bias in the final comparison between intervention and control groups. In this case, all the estimations would be expressed as odds ratios with 95% confidence intervals.

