## Discussion

The role of primary care in the early diagnosis of COPD is indisputable, as is the need for spirometry testing to diagnose this condition [25]. This technique is currently well established in primary care consultations, the quality of the tests having greatly improved in this level of care [24]. On the other hand, the early diagnosis of COPD by spirometry is still somewhat controversial. Assuming that most of the diagnoses would be mild or moderate COPD, the most important measure to improve morbidity and mortality would be smoking cessation and, as we have noted, very few high quality studies have assessed the independent role of spirometry for achieving this objective[14,16]. Of all the studies identified, only two investigated the independent role of spirometry for smoking cessation and both reached negative conclusions [15,26]. More recently, in 2008, Parkes et al. [20] found that by presenting spirometry results in terms of “lung age” there was a greater decrease in smoking than in a control group who were presented the results in the usual way. Nevertheless, this study does not fully clarify the role of spirometry as testing was performed for both groups. Some previous observational studies [27,28] have found higher quit rates in patients diagnosed with COPD. On the other hand, in order to achieve good results in COPD screening, the increase in quit rates would need go beyond the patients with a new diagnosis of COPD, and extend to smokers in general; this is because if there were higher quit rates in COPD patients without a parallel increase across all the smokers analyzed, the intervention would lose some of its value, since we could assume that the absence of effectiveness were due to the potential reassuring effect for many smokers of discovering that they have “normal” lung function. For this reason, the primary objective of our study is to assess whether performing spirometry and informing patients of the results increases the quit rate in smokers over 40 years of age with a smoking history of more than 10 pack-years, whether they have COPD or not, the secondary objectives being to achieve smoking cessation in those with COPD and decrease the consumption of cigarettes in those who continue to smoke.

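### The secondary cigarettes/day outcome is restricted to patients still smoking, so its between-arm test is not a randomised comparison and carries a bias of unknown size and sign

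*Protocol article*

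**What the plan says.** Four sections of the protocol article bear on this outcome.

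- **Objectives** gives a secondary objective of "comparing the change in daily smoking rate between the intervention and control groups". It concerns change, and it is not limited to any subset.
- **Study variables** names the outcome itself: "the secondary outcome variable will be the number of cigarettes/day for those who continue smoking". This is a level, in a subset. The same section fixes the variable that forms the subset: "The primary outcome variable will be smoking cessation 1 year after the intervention".
- **Discussion** words the secondary aim as to "decrease the consumption of cigarettes in those who continue to smoke", which is again the subset.
- **Statistical analysis** says "Data will be analyzed on an intention-to-treat basis" and, for outcomes of this type, "Continuous variables will be assessed with the Student’s t-test, if the data meet the assumption of normality", with a non-parametric test otherwise. Its only adjustment method is logistic regression for the primary outcome. It does not say how quitters enter the cigarettes/day comparison.

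**The concern.** Whether a patient still smokes at 1 year is settled after randomisation, and it is what the intervention is meant to change. If the intervention works, it removes more patients from the experimental arm than from the control arm, and not necessarily patients of the same kind. The smokers who remain are then no longer exchangeable between arms. A t-test on them mixes any effect on consumption with the effect of who has left.

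At stake is the interpretation of the one variable that the article names as its secondary outcome. A difference in either direction could come from selection alone, and so could the absence of one. This is a stated outcome definition that conflicts with the stated objective and analysis principle, not a detail left to a document that is not shown.

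**Working it through.** **1. The plan's own figure.** Inputs from the sample size paragraph of Methods/Design: quit rates 5% and 14%, two-sided 5% significance level, 80% power, 1:1 allocation, 25% loss. With a mean rate of 0.095:

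n = [1.960 × √(2 × 0.095 × 0.905) + 0.842 × √(0.05 × 0.95 + 0.14 × 0.86)]² / 0.09² = 165.4, so 166 per arm.

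166 / 0.75 = 221.3, so 222 per arm and 444 in total. This agrees with the article, which gives no figure for cigarettes/day.

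**2. Who is compared.** Of 166 evaluable patients per arm, the restricted comparison keeps 166 × 0.95 = 158 controls and 166 × 0.86 = 143 experimental patients.

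**3. Size and sign, as a level.** The following are assumptions, since the article has no consumption data. Mean consumption would be 20/day in both arms if nobody quit. Those who quit would otherwise have averaged q/day, the same in both arms. The intervention does nothing except raise quitting from 5% to 14%.

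- Continuing smokers: control (20 − 0.05q)/0.95, experimental (20 − 0.14q)/0.86.
- All patients, quitters at 0: control 20 − 0.05q, experimental 20 − 0.14q, difference −0.09q.

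| q | Control, still smoking | Experimental, still smoking | Difference | All-patient difference |
|---|---|---|---|---|
| 5 | 20.79 | 22.44 | +1.65 | −0.45 |
| 10 | 20.53 | 21.63 | +1.10 | −0.90 |
| 15 | 20.26 | 20.81 | +0.55 | −1.35 |
| 20 | 20.00 | 20.00 | 0.00 | −1.80 |
| 25 | 19.74 | 19.19 | −0.55 | −2.25 |

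A positive difference is against the intervention. In every row nobody smokes more because of the intervention and the additional quitters go to zero, yet the restricted difference takes either sign. The all-patient difference does not.

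**4. On the change scale of the Objectives.** If q differs from 20 only because quitters smoked less or more at baseline, and continuing smokers do not change, the restricted difference in change is 0. A bias remains if quitters would otherwise have changed their consumption differently from the rest. Suppose the 86% who smoke under either allocation cut 1/day, and the 9% induced to quit would otherwise have cut c. Control is then −(0.86 × 1 + 0.09c)/0.95 and experimental is −1.

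- c = 4: control −1.28, difference +0.28
- c = 6: control −1.47, difference +0.47
- c = 8: control −1.66, difference +0.66
- c = 0: control −0.91, difference −0.09

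The sign again depends on who quits. In all patients the expected difference in change equals the expected difference in level, because randomisation gives both arms the same expected baseline. The −0.09q column therefore carries over.

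**5. Effect on the test.** A simulation used 4,000 trials, 166 per arm, mean 20 and SD 8 (both assumed), a t-test on the level, and no effect on continuing smokers. With quitting unrelated to consumption, a significant result favoured control in 2.6% of trials (nominal 2.5%). With the odds of quitting 1.6 to 4.5 times higher per SD lighter, the mean difference was +0.33 to +0.78/day and the figure was 5.5% to 14.3%.

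**The case against.** The strongest reply is that cutting down among people who still smoke is a legitimate clinical question, and that scoring quitters as 0 replaces it with a composite that quitting dominates. In the table above, the whole all-patient difference comes from quitting. That is correct, and it is why the continuing-smoker figure should stay. What it does not support is reading an unadjusted test in that subset as an effect of allocation.

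The Objectives and Study variables sections can also be read together, one naming the comparison and the other its population. That removes the contradiction in wording, but the comparison then remains restricted and non-randomised.

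A reader might infer that the restriction works against the intervention and could contradict a true primary benefit. The documents do not support a direction. They give no consumption figures, and the Discussion points, if anywhere, the other way. It reports higher quit rates after a COPD diagnosis, a possible reassuring effect of normal results, and a COPD risk that rises with cumulative smoking. On that account the induced quitters could be heavier smokers. The shifts are also modest against the noise: with 158 and 143 patients and an assumed SD of 10, the standard error is 10 × √(1/158 + 1/143) = 1.15/day.

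Two further criticisms are tempting and should not be pressed. Table 1 says "Any patient who smokes one or more cigarettes per day will be considered an active smoker", but that wording serves eligibility. Quitting is defined separately, and a patient on less than one a day has not met that definition, so is most naturally a continuing smoker. The article is also silent on what is asked of a patient who claims to have quit and fails the CO test, but that is data-collection detail an article may leave out.

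**Conclusion.** The concern holds for the secondary outcome as defined. The subset is formed by the primary outcome, and the protocol's own rates predict unequal selection (95% against 86% retained). The between-arm test is therefore not a randomised comparison, and it matches neither the unrestricted objective nor the intention-to-treat statement.

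Under the labelled assumptions the bias on the level scale runs from +1.65 to −0.55/day and is zero if quitting is unrelated to consumption. On the change scale it was +0.66 to −0.09 in the cases shown. These ranges illustrate the problem and do not predict the trial's result. An unknown sign is itself a reason to act, since a result in either direction could not be interpreted. The primary analysis, the sample size and the article's conclusions about quit rates are untouched, so this should be corrected but does not threaten the trial's main answer.

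**What to change.** Define the secondary outcome, in line with the Objectives, as change in cigarettes/day from baseline to 1 year, compared by allocated arm in all randomised patients, with CO-confirmed abstainers counted as 0 cigarettes/day. Reword the Study variables and Discussion sentences to match. Report the figure for continuing smokers beside it as descriptive, with no between-arm causal claim.

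The cost is a few sentences. The outcome then combines quitting with cutting down and overlaps with the primary outcome, which is why the descriptive figure stays. Abstainers will form a cluster of large reductions, for which the article's non-parametric option is already available. The change does not settle how the assumed 25% lost to follow-up are handled. The full protocol or analysis plan may do so, and its rule should cover this outcome too.

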### Statistical analysis

Data will be analyzed on an intention-to-treat basis using SPSS 19.0 software. Given that the primary outcome measure is categorical in nature (whether patients do or do not quit smoking), the final comparison will be performed using chi-squared tests and effect size estimates will be expressed as relative risk (RR), absolute risk reduction (ARR), and number needed to treat (NNT) with the corresponding 95% confidence interval (95% CI). Continuous variables will be assessed with the Student’s t-test, if the data meet the assumption of normality, and otherwise with the corresponding non-parametric test.

If this initial analysis demonstrates the need for multivariate analysis, binary logistic regression analysis will be used. This type of model will allow us to compare the primary outcome measure between groups adjusting for any observed differences, and thus minimizing the potential for confounding bias in the final comparison between intervention and control groups. In this case, all the estimations would be expressed as odds ratios with 95% confidence intervals.

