A sample of 444 people will be recruited. The sample size calculation was based on assuming a level of significance of 5%, a quit rate after brief anti-smoking intervention only (control group) of 5% [23], an expected quit rate in the experimental group of 14% [20], and a 1:1 ratio of control to experimental subjects. Given these premises, to obtain a power of 80% to detect differences in the test of the null hypothesis Ho: p1 = p2 using a two-tailed chi-squared test for two independent samples, it would be necessary to include 166 experimental units in the reference group and a further 166 in the experimental group, making a total of 332 units for the study. Assuming a loss to follow-up of 25%, it would be necessary to recruit 222 subjects for the reference group and a further 222 for the experimental group, summing to the aforementioned total of 444 subjects for the study. The flow chart for the study is presented in Figure 1.

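### Daily smoking is to be tested without adjustment for baseline consumption, and the article names two different quantities to compare; the rule is valid but inefficient

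*Protocol article*

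**What the plan says.** All references are to the protocol article.

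- **Objectives** lists among the secondary aims "comparing the change in daily smoking rate between the intervention and control groups".
- **Study variables** says instead that "the secondary outcome variable will be the number of cigarettes/day for those who continue smoking". It does not mention change and gives this outcome no time point of its own; 1 year is inferred from the primary outcome in the same sentence.
- **Statistical analysis** gives one rule for all such outcomes: a t-test "if the data meet the assumption of normality, and otherwise with the corresponding non-parametric test".
- The only adjusted model in that section is a logistic regression, used if the first analysis shows a need. It serves the quit outcome alone: "This type of model will allow us to compare the primary outcome measure between groups adjusting for any observed differences". The effect measures named there (relative risk, absolute risk reduction, number needed to treat, odds ratio) are likewise those of a binary outcome.

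**The concern.** Two things are fixed badly.

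First, the endpoint is unsettled. Change from baseline and the 1-year value are different variables with different variances, and the analysis section does not choose between them.

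Second, under either reading the prescribed test is an unadjusted two-group comparison. Baseline consumption must be known for change to be computed at all, and it is likely to predict later consumption. A model with baseline as a covariate uses that information better than the raw 1-year value or a simple difference. It also makes the choice between the two readings matter less: with baseline as a covariate on the same scale, the 1-year value and the change give the same treatment effect.

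At stake is the power of a declared secondary objective, and whether its result comes with one effect measure fixed in advance.

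**Working it through.** **1. The plan's own figure.** Inputs from Methods/Design: quit rates of 5% and 14%, two-sided 5% level, 80% power, 1:1 allocation, 25% loss. With mean rate 0.095:

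n = [1.96·√(2·0.095·0.905) + 0.842·√(0.05·0.95 + 0.14·0.86)]² / 0.09² = 165.4, so 166 per arm; 166/0.75 = 221.3, so 222 per arm and 444 in total.

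The stated figures reproduce. They concern the quit outcome only. No SD, correlation or effect size is given for cigarettes/day, so everything below rests on assumed values shown as ranges.

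**2. Patients available.** Of 166 followed per arm, continuing smokers number 166 × 0.95 ≈ 158 (control) and 166 × 0.86 ≈ 143 (intervention). The equivalent equal-arm size is 2/(1/158 + 1/143) = 150.1.

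**3. Normal approximation.** Let ρ be the correlation between baseline and 1 year, with equal variance σ² at both times. The variance per patient is σ² for the 1-year value, 2(1−ρ)σ² for change and (1−ρ²)σ² after baseline adjustment. The rank test is given relative efficiency 0.955. The effect is set so that a t-test on the 1-year value has 50% power: 1.96·√(2/150.1) = 0.226 SD.

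| ρ (assumed) | Variance ratio, 1-year value : adjusted | Variance ratio, change : adjusted | Power: rank on value / rank on change / adjusted |
|---|---|---|---|
| 0.3 | 1.10 | 1.54 | 48 / 37 / 54% |
| 0.5 | 1.33 | 1.33 | 48 / 48 / 62% |
| 0.7 | 1.96 | 1.18 | 48 / 70 / 78% |
| 0.8 | 2.78 | 1.11 | 48 / 86 / 90% |

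**4. Skewed, rounded counts, adjusted on the raw scale.** Assumed: log-normal consumption with log SD 0.5, larger values rounded to multiples of 5, 158 and 143 patients, 12% reduction, 1,500 runs per setting. A Shapiro-Wilk check at 5% rejected normality in every run, for the value and for the change, so the rule became a rank test. With no effect, the two-stage rule rejected in 3.6 to 5.5% of runs. Power (rank on value / rank on change / raw-scale adjusted) was:

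- ρ 0.3: 57 / 35 / 58%
- ρ 0.5: 56 / 44 / 64%
- ρ 0.7: 56 / 64 / 78%
- ρ 0.8: 56 / 77 / 87%

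**5. Heavier skew, still on the raw scale.** Assumed: 150 per arm, 70% of values rounded to multiples of 5, robust standard errors. Same order of methods:

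- log SD 0.7, 17% reduction: 61 / 43 / 57% (ρ 0.3); 59 / 51 / 60% (ρ 0.5)
- log SD 0.8, 20% reduction: 64 / 42 / 56% (ρ 0.3); 64 / 52 / 60% (ρ 0.5); 63 / 73 / 73% (ρ 0.7)

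Here raw-scale adjustment ties with, or loses to, the better of the two rank tests.

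**6. Adjustment on the log scale.** With 158 and 143 patients, log SD 0.5 to 0.8 and ρ 0.3 to 0.7, adjustment on the log or rank scale beat both unadjusted rank tests in every setting: 61 to 90% against 38 to 77%. On the log scale the gain was about 6 to 25 points over the rank test on the 1-year value and about 12 to 27 over the rank test on change. In the same runs the raw-scale model at log SD 0.8 and ρ 0.3 had 57% against 65% for the rank test on the value. Type I error under the current rule was again 3 to 5%.

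**The case against.** The best defence is that a t-test or rank test is a conventional, valid choice for a secondary outcome. Type I error is sound, and a condensed article may leave covariates to a fuller document. Validity is conceded. The appeal to condensation is weaker, because the article states a rule for continuous variables, which a later plan would have to overturn and not merely fill in.

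Four stronger readings are tempting, and the documents do not support them.

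- *The plan ignores each patient's starting level.* Objectives names change, and a change score uses the starting level. What can be said is that no adjustment is prescribed and that the two sections disagree.
- *Only a p-value will be reported.* That is read from silence. The article does not say so, and a rank test does not prevent a mean or median difference from being given.
- *The data will choose the hypothesis.* Formally they do, but no normality check is named. If a formal test almost always rejects, the rule is in effect one fixed rank test.
- *The power loss is clear and costs nothing to recover.* It depends on a skew and correlation the documents do not give. At ρ 0.3 and log SD 0.5 the raw-scale gain over the rank test on the 1-year value is 1 point (57 to 58%), and under heavy skew it can be negative.

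**Conclusion.** The point holds as one of efficiency and of an unsettled endpoint, not of validity. Objectives and Study variables must be reconciled, and an unadjusted test is a poorer choice than a baseline-adjusted model on a suitable scale. The expected gain is about 6 to 25 power points against the rank test on the 1-year value and about 12 to 27 against the rank test on change.

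These sizes rest on assumed log-normal consumption, a proportional effect, log SD 0.5 to 0.8 and ρ 0.3 to 0.7. The first two assumptions favour the log scale, and the gain over the change score shifts by several points with the rounding and averages assumed. The direction is firmer than the exact size. Only a secondary objective is affected; the quit-rate comparison and the 444 patients stand.

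**What to change.** 1. Reconcile Objectives and Study variables: state whether the secondary endpoint is change or the 1-year number of cigarettes/day, at what time, and in whom.
2. Drop the normality switch for this outcome. Among continuing smokers, prespecify one model: log cigarettes/day at 1 year on arm and log baseline cigarettes/day, with robust standard errors. Report the adjusted ratio, read as a percentage difference, with its 95% CI.
3. Give the raw-scale adjusted mean difference with 95% CI, and the rank test, as supportive analyses.
4. Say how a report of zero cigarettes is handled when exhaled CO does not confirm quitting, because its logarithm is undefined.

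The cost is a few sentences of analysis wording, with no extra patients or visits. There are two downsides. The main effect becomes a ratio and not a number of cigarettes, which the supportive mean difference offsets. And because the comparison is confined to continuing smokers, with different expected quit rates in the two arms, baseline adjustment reduces selection but does not remove it.
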